### Provisions for post-trial care {30}

Post-trial care is the responsibility of the treating clinicians; Ancillary and post-trial care are not planned. If a participant experiences an adverse event following immunisation after the trial, they should seek medical review from their primary care clinician or the emergency department, as appropriate. Noting that trial follow-up continues for 12 months after COVID-19 vaccines have been completed.

### Outcomes {12}

The primary outcome is defined as the geometric mean concentration (GMC) of anti-spike IgG antibody against SARS-CoV-2, 28 days after completion of trial vaccine/s, i.e. after one or two doses in the respective trial arms.

Secondary outcomes include laboratory, safety and clinical outcomes:

Laboratory outcomesThe GMC of anti-spike IgG antibody against SARS-CoV-2, 6 and 12 months after completion of trial vaccine/sThe proportion of participants seropositive to SARS-CoV-2 IgG, 1, 6 and 12 months after completion of trial vaccine/sThe GMC of anti-spike IgG antibody targeting specific SARS-CoV-2 variants, 1, 6 and 12 months after completion of trial vaccine/sThe SARS-CoV-2 neutralising antibody response, 1, 6 and 12 months post completion of trial vaccine/s, in a subset of participants with response defined as either rise in the neutralising antibody titreο Fourfold rise in the neutralising antibody titre for those with detectable neutralising antibodies at baseline, ORο Detectable neutralisation in those with no detectable neutralising antibodies at baselineThe magnitude of SARS-CoV-2 specific T-cell responses, 1, 6 and 12 months post completion of trial vaccine/s in a subset of participantsSubset analysis and polyfunctionality (number of effector cytokines) of SARS-CoV-2 specific T-cell responses, 1, 6 and 12 months post completion of trial vaccine/s in a subset of participants

Safety outcomesLocal and systemic reactions assessed on days 1, 2, 3, 4, 5, 6 and 7 after randomisation.Hospitalisation resulting from adverse events following immunisation (AEFI) up to day 28.Adverse events of special interest (AESI) up to 12 months post completion of trial vaccine/s

Clinical outcomesHistory of PCR-confirmed OR rapid antigen test (RAT) positive SARS-CoV-2 infection in participants up to 12 months post completion of trial vaccine/sPCR-confirmed OR rapid antigen test (RAT) positive SARS-CoV-2 infection requiring attendance at a medical facility for assessment and/or hospital admission up to 12 months post completion of trial vaccine/sMortality due to any cause up to 12 months post completion of trial interventionMortality due to SARS-CoV-2 infection up to 12 months post completion of trial interventionNeed for oxygen therapy and/or ventilatory support due to SARS-CoV-2 infection up to 12 months post completion of trial vaccine/sNeed for ICU care due to SARS-CoV-2 infection up to 12 months post completion of trial vaccine/sQuality of life estimates (EQ-5D-5L) at 1, 6 and 12 months post completion of trial vaccine/sHealthcare utilisation including outpatient pharmaceutical and medical service use and inpatient hospital admissions related to COVID-19 and study vaccines.

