**Fig. 1 Fig1:**
[figure not shown]
Trial design if **a**) one COVID-19 vaccine is included in the trial, **b**) if two COVID-19 vaccines are included in the trial, and **c**) if three COVID-19 vaccines are included in the trial

**Table 1 Tab1:** Schedule of activities

Protocol activities										
	**Visit 1**^**c**^ **Screening**	**Visit 2**^**c**^ **Baseline**	**Visit 3**	**Visit 4 **^**a**^	**Visit 5**^**a**^	**Visit 6**^**b**^	**Visit 7**^**a**^	**Visit 8**^**b**^	**Visit 9**^**a**^	**Unscheduled visit **^**f**^
Visit window	Up to 4 weeks pre M0	M0	M1 (D28) + / − 7 days	M3 (D84) + / − 7 days	M4 (D112) + / − 7 days	M6 (D180) + / − 30 days	M9 (D 270) + / − 30 days	M12 (D 365) + / − 30 days	M15 (D455) + / − 30 days	
Informed consent	✓									
Medical history, incl/excl criteria	✓									
Symptoms, adverse events,		✓	✓	✓	✓	✓	✓	✓	✓	✓
QOL		✓	✓		✓	✓	✓	✓	✓	✓
Vaccine administered		✓		✓						
SARS-CoV-2 IgG assessment		✓^**d**^	✓^**d**^	✓^**d**^	✓^**d**^	✓^**d**^	✓^**d**^	✓^**d**^	✓^**d**^	✓^**d**^
Blood to process and store as plasma and PBMCs^e^		✓	✓	✓	✓	✓	✓	✓	✓	✓

Notes: *M* month, *QOL* quality of life, *PBMCs* peripheral blood mononuclear cells

^a^ If randomised to a second study vaccine

^b^ If only receiving one study vaccine

^c^ Screening and baseline procedures can be completed on the same day

^d^ Quantitative ELISA for SARS-CoV-2 anti-spike IgG

^e^ Immunogenicity subset including SARS-CoV-2 neutralisation assay (see section below)

^f^ An example of an unscheduled visit is for individuals receiving anti-SARS-CoV-2 monoclonal antibodies on study and attending for additional assessment of SARS-CoV-2 IgG, ideally in the 3 days before and 3 days after the infusions to assess antibody kinetics

After receipt of each vaccine, participants will be asked to complete a survey on a secure web-based portal regarding their experience of local and systemic reactions following the trial intervention, daily for 7 days.

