### Sample size {14}

The maximum sample size is 960 participants, including 320 in each of the HIV, SOT, and haematological malignancy groups. This maximum sample size is based on simulations conducted prior to trial commencement for estimating the primary outcome (anti-spike SARS-CoV-2 IgG antibodies 28 days after completion of trial vaccine/s) for different trial strata (clinical group [HIV, SOT, haematological malignancy], vaccine brand, SARS-CoV-2 serostatus at enrolment) with sufficient precision. The simulations are detailed in the Statistical Appendix and will be published separately.

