## Statistical methods

### Statistical methods for primary and secondary outcomes {20a}

Baseline demographic and anthropometric data as well as the defined safety and immunogenicity outcome measures will be stratified by study cohort (HIV, SOT, haematological malignancy) and summarised with appropriate measures of spread. Immune responses and reactogenicity to COVID-19 vaccines will be assessed on a modified intention-to-treat population, depending on actual intervention received between randomisation and providing blood samples for the primary endpoint. Participants with SARS-CoV-2 infection or antibody therapy (e.g. IVIG), between randomisation and providing blood samples will be excluded from the primary analysis. For safety reporting, participants will be included in the intervention group that they received, irrespective of the intervention they were randomised to.

The primary outcome will be the anti-spike IgG antibody against SARS-CoV-2, 21–35 days after completion of study vaccines, summarised as the GMC. Participants who miss a study blood draw, have SARS-COV-2 infection diagnosed by RAT, PCR or anti-nucleocapsid antibodies, or obtain an unscheduled dose of COVID-19 vaccine between the time of randomisation and the primary endpoint will be excluded from analysis. A Bayesian hierarchical two-part model will be used for the primary analysis as it is anticipated that a significant proportion of primary outcomes may be below the assay limit of detection.

Secondary endpoints described above will be analysed depending on the type of outcome; continuous immunological variables will be modelled with the two-part Bayesian model described; binary endpoints, including safety endpoints, will be analysed using a Bayesian logistic model; a Bayesian Poisson regression will be used to compare counts and rates. Further statistical detail is available in the statistical appendix which will be published separately.

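### Neutralisation is listed only as a yes/no response at 1, 6 and 12 months; a baseline-adjusted geometric mean titre should be the outcome, with the responder proportion in support

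*Protocol article*

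**What the plan says.** Outcomes {12} in the protocol article lists one neutralisation outcome, in a subset of participants, at 1, 6 and 12 months after the last trial vaccine. It is a response with two routes: "Fourfold rise in the neutralising antibody titre for those with detectable neutralising antibodies at baseline", or "Detectable neutralisation in those with no detectable neutralising antibodies" at baseline. No neutralising geometric mean titre is listed. In the same list, anti-spike IgG has a geometric mean concentration and a proportion seropositive, variant-specific IgG has a geometric mean concentration, and T-cell responses are described by magnitude.

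Statistical methods {20a} assigns models by type of outcome: "binary endpoints, including safety endpoints, will be analysed using a Bayesian logistic model", and "continuous immunological variables will be modelled with the two-part Bayesian model described". A footnote to Table 1 describes the assayed group only as "Immunogenicity subset including SARS-CoV-2 neutralisation assay". Sample size {14} concerns the primary outcome alone: "The maximum sample size is 960 participants, including 320 in each of the HIV, SOT, and haematological malignancy groups".

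**The concern.** A fourfold-rise rule can be applied only once the baseline and follow-up titres are known. The trial will therefore hold quantitative neutralisation data, yet the outcome as listed reduces them to yes or no before modelling. Among the antibody outcomes, only neutralisation has no quantitative summary in the list.

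Two features raise the cost. The assay is run only in a subset, so the sample is smaller than the trial's. And the rule is anchored to baseline and carried unchanged to 12 months, where it serves as a measure of durability. If titres fall back towards baseline, a fourfold threshold sits far out in the distribution and separates regimens poorly. At stake is a real difference between regimens in neutralisation, which bears on the correlates of protective immunity named in Objectives {7}, being reported as inconclusive.

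**Working it through.** **Inputs.** The document supplies the two-route rule, the time points and the model classes. It gives no subset size, titre SD, response rate, share undetectable at baseline or decline over time, so there is no figure of the plan's own to reproduce. Every number below is an assumption or follows from one.

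**Step 1: fourfold route alone, normal log fold-rise, small effects.** The information kept by a cut with responder proportion p is φ(z_p)² / [p(1−p)], where z_p is the normal quantile and φ the normal density. At p = 0.5 this is 0.3989² / 0.25 = 0.637, a loss of 36.3%.

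| Responders | 50% | 40% | 30% | 20% | 10% | 5% |
|---|---|---|---|---|---|---|
| Information lost | 36.3% | 37.8% | 42.4% | 51.0% | 65.8% | 77.6% |

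**Step 2: how many would respond on that route.** p = 1 − Φ[(log10 4 − log10 F)/SD], with F the geometric mean fold-rise. With log10 SD 0.5, F = 1 gives 1 − Φ(0.602/0.5) = 11%, F = 2 gives 27%, F = 3 gives 40% and F = 4 gives 50%. Whether responders are rare at 6 and 12 months depends on F, which the article does not give.

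**Step 3: the same loss as sample size.** Assume log10 SD 0.5, a between-arm ratio of 1.5, two-sided 5% and 80% power. The continuous analysis needs 2 × (1.960 + 0.842)² × 0.5² / (log10 1.5)² = 127 per arm. The responder analysis needs 201 per arm at a 40% control response, 237 at 20% and 320 at 10%. The losses are 1 − 127/201 = 37%, 1 − 127/237 = 46% and 1 − 127/320 = 60%. Power serves here only as a yardstick for information; the plan is Bayesian and states no power.

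**Step 4: the rule as written.** Simulation with both routes and censoring at the detection limit. Assumptions: log10 baseline SD 0.6, log10 change SD 0.5, between-arm ratio 1.5, and 10-70% undetectable at baseline. The table gives the information lost by the responder comparison against log titre adjusted for baseline, by geometric mean fold-rise in the lower arm.

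| Undetectable at baseline | F = 1 | 1.58 | 2.51 | 3.98 | 7.94 |
|---|---|---|---|---|---|
| 10% | 57% | 43% | 39% | 38% | 50% |
| 30% | 50% | 42% | 36% | 39% | 51% |
| 50% | 42% | 36% | 33% | 37% | 49% |
| 70% | 33% | 27% | 29% | 34% | 48% |

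The loss runs from 27% to 57%. It shrinks as more participants start undetectable, because the second route and censoring leave less quantitative information to discard. An independent repeat of the simulation gave closely similar values. Adjusting the responder analysis for baseline recovered little.

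**Step 5: adjustment is what makes the gain.** Against follow-up log titre *without* baseline adjustment, the same calculation runs from −48% to +12%, and it is negative in 19 of the 20 scenarios. Under these assumptions the responder rule, which uses the baseline value, usually beats an unadjusted geometric mean titre. Adding the titre without baseline adjustment would therefore not be an improvement.

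**The case against.** The strongest case on the other side has five parts.

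- **The rest may be in the appendix.** This is a condensed article, and supplementary titre summaries may sit in the statistical appendix, which is not shown. This limits the point: the binary definition can be asserted only of the article's own outcome list, and a reader should not infer that titres will never be analysed. The list does fix the outcome, however, and the methods section fixes the model class for it.
- **The second route is needed.** No fold-rise can be calculated from an undetectable baseline, and baseline status precedes randomisation, so the two bars do not bias the comparison of arms. This stands. The two routes are not an error, though they pool different events in one proportion.
- **Few responders at 6 and 12 months is not shown.** A reader might infer this from the 3 to 7 earlier doses and expected waning. The article has no neutralisation or waning data, and it expects that many binding IgG values may be below detection, so many participants might qualify by new detectability. This stands; rarity is a possibility only.
- **No single loss figure belongs to the plan.** A reader might take the fourfold route alone and quote a loss such as 37-69%. In Step 1 that range corresponds to assumed responder proportions of about 43% down to 8.4%. It leaves out the second route and censoring and has no input in the document.
- **It is a secondary outcome with no power claim.** True. The trial is sized for precision of the primary outcome, which is untouched.

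None of this restores the information lost by the cut.

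**Conclusion.** The point holds in limited form. As listed in the article, the subset neutralisation outcome is binary at all three times and goes to the logistic model, although the titres exist and a model for continuous immunological data is already planned. With the two-route rule and censoring, the loss relative to baseline-adjusted log titre is roughly 27-57%. This assumes log10 SDs of 0.6 (baseline) and 0.5 (change), a 1.5-fold difference between arms and 10-70% undetectable at baseline. If responders prove rare the loss could be larger; the fourfold route alone gives 66% at 10% responders and 78% at 5%. The comparator in the simulation was a baseline-adjusted analysis of log titre, not the two-part Bayesian model itself, so the range indicates the gain to expect and is not a forecast for this trial. The change is worth making but is not critical.

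**What to change.** In Outcomes {12}, make the neutralisation outcome the geometric mean neutralising titre at 1, 6 and 12 months after the last trial vaccine. In Statistical methods {20a}, state that it is analysed on the log scale with the two-part Bayesian model already planned for continuous immunological variables, adjusted for baseline neutralising titre with an indicator for undetectable at baseline. Keep the two-route responder proportion, with its logistic model, as a supportive summary at the same times. The baseline terms are essential, for the reason in Step 5.

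The cost is small: one secondary outcome reworded before its analysis, with the ethics committee approval and registry update that the article's section on amendments {25} requires. It needs no new samples, visits or assays and no new class of model.

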### Participant timeline {13}

The study design and participant timeline are detailed in Fig. 1 and encompass a minimum of 1 and a maximum of 3 different study vaccines. Table 1 details the schedule of activities. Participants will have up to 7 visits during the study period, with follow-up continuing for 12 months following their final study vaccine. Participants randomised to receive one study vaccine will have 5 study visits, while those randomised to two doses of vaccine will have 7 visits. Participants following assigned study procedures can remain on the study for 13 to 16 months.

**Fig. 1 Fig1:**
[figure not shown]
Trial design if **a**) one COVID-19 vaccine is included in the trial, **b**) if two COVID-19 vaccines are included in the trial, and **c**) if three COVID-19 vaccines are included in the trial

**Table 1 Tab1:** Schedule of activities

Protocol activities										
	**Visit 1**^**c**^ **Screening**	**Visit 2**^**c**^ **Baseline**	**Visit 3**	**Visit 4 **^**a**^	**Visit 5**^**a**^	**Visit 6**^**b**^	**Visit 7**^**a**^	**Visit 8**^**b**^	**Visit 9**^**a**^	**Unscheduled visit **^**f**^
Visit window	Up to 4 weeks pre M0	M0	M1 (D28) + / − 7 days	M3 (D84) + / − 7 days	M4 (D112) + / − 7 days	M6 (D180) + / − 30 days	M9 (D 270) + / − 30 days	M12 (D 365) + / − 30 days	M15 (D455) + / − 30 days	
Informed consent	✓									
Medical history, incl/excl criteria	✓									
Symptoms, adverse events,		✓	✓	✓	✓	✓	✓	✓	✓	✓
QOL		✓	✓		✓	✓	✓	✓	✓	✓
Vaccine administered		✓		✓						
SARS-CoV-2 IgG assessment		✓^**d**^	✓^**d**^	✓^**d**^	✓^**d**^	✓^**d**^	✓^**d**^	✓^**d**^	✓^**d**^	✓^**d**^
Blood to process and store as plasma and PBMCs^e^		✓	✓	✓	✓	✓	✓	✓	✓	✓

Notes: *M* month, *QOL* quality of life, *PBMCs* peripheral blood mononuclear cells

^a^ If randomised to a second study vaccine

^b^ If only receiving one study vaccine

^c^ Screening and baseline procedures can be completed on the same day

^d^ Quantitative ELISA for SARS-CoV-2 anti-spike IgG

^e^ Immunogenicity subset including SARS-CoV-2 neutralisation assay (see section below)

^f^ An example of an unscheduled visit is for individuals receiving anti-SARS-CoV-2 monoclonal antibodies on study and attending for additional assessment of SARS-CoV-2 IgG, ideally in the 3 days before and 3 days after the infusions to assess antibody kinetics

After receipt of each vaccine, participants will be asked to complete a survey on a secure web-based portal regarding their experience of local and systemic reactions following the trial intervention, daily for 7 days.

### Sample size {14}

The maximum sample size is 960 participants, including 320 in each of the HIV, SOT, and haematological malignancy groups. This maximum sample size is based on simulations conducted prior to trial commencement for estimating the primary outcome (anti-spike SARS-CoV-2 IgG antibodies 28 days after completion of trial vaccine/s) for different trial strata (clinical group [HIV, SOT, haematological malignancy], vaccine brand, SARS-CoV-2 serostatus at enrolment) with sufficient precision. The simulations are detailed in the Statistical Appendix and will be published separately.

### Recruitment {15}

Research staff at participating sites will be trained on trial requirements to ensure eligible participants are identified, provided with appropriate information, and invited to participate in the trial. Eligible participants are identified across participating sites by clinicians involved in the care of eligible patient groups in the inpatient and ambulatory setting. Recruitment strategies will use approved material to target the study population and specific subgroups of participants based on medical and COVID-19 vaccination history.

## Assignment of interventions: allocation

### Sequence generation {16a}

Participants will be assigned to an arm using a central computer-generated random allocation algorithm. Randomisation will be stratified by study subgroup (HIV, SOT, haematological malignancy).

Participants will be equally randomised to one of the available vaccine arms if an intervention arm is dropped after an interim analysis or following a recommendation from the data safety management committee, then future participants will be equally allocated to the remaining arms.

### Concealment mechanism {16b}

After central randomisation, individual assignments will be delivered securely and confidentially to the identified unblinded site personnel administering the vaccines via a web-based portal and dispensed from an onsite clinical trials pharmacy by an unblinded pharmacist. At vaccination, an un-blinded member of the research team will dispense and administer the study vaccine to a blinded participant. Pre-filled syringes containing an allocated approved COVID-19 booster vaccine will be covered with opaque tape and concealed in an opaque box until ready for administration. Prior to opening the box, the participant will be asked to look away. The member of the research team will administer the trial vaccine per Australian guidelines.

### Implementation {16c}

Participants will be enrolled by the research team and will be randomly assigned to interventions as described, using an allocation sequence generated by study statisticians. Trial vaccines will be administered as described, to ensure allocation concealment.

## Assignment of interventions: blinding

### Who will be blinded {17a}

Participants and clinicians involved in their care will be blinded to intervention allocation, though will become unblinded to the administration of a second study vaccine dose after the 1-month visit. This is because immunisations administered to participants over the duration of the study need to be recorded on the Australian Immunisation Register (AIR) by the un-blinded vaccine nurse. The type and date of the vaccine administered will be recorded in the study database and uploaded to AIR 6 weeks following randomisation. As participants are then able to look up their study vaccine on the AIR, they have the potential to become unblinded from this point onwards.

Research staff involved in the follow-up of adverse reactions will be blinded to the group assignment of the participants. Laboratory staff processing or analysing trial specimens will be blinded to the group assignment of participants.

Trial Pharmacists, preparing interventions, research staff administering vaccine doses, and a nominated trial statistician who will prepare interim reports for the data safety and monitoring committee will be unblinded.

### Procedure for unblinding if needed {17b}

In the event of compelling medical, safety or other concerns, a central password-protected randomisation list can be accessed by the trial statistician, upon authorisation by the principal investigator or their delegate, during business hours. Participants for whom the assignment is revealed will remain in the study and where possible continue to receive surveys and attend scheduled study visits.

## Data collection and management

### Plans for assessment and collection of outcomes {18a}

After enrollment, research nurses will collect relevant demographic (age, sex and ethnicity) and clinical data (comorbidities, immunosuppression, and COVID-19 vaccination and infection), in accordance with a trial-specific case report form (CRF) at the baseline visit. Participants are scheduled for either 5 or 7 trial visits (Table 1), depending on whether randomised to one or two vaccine booster doses. From day 1 to 7 following study vaccine administration, participants will be asked to complete a daily electronic vaccine diary card delivered via email or text message.

Table 1 outlines the study schedule. Blood samples will be collected at baseline and each follow-up visit, for assessment of immunological outcomes. At each study visit, a research nurse will collect relevant clinical data per the CRF, review incomplete diary card entries as appropriate, and assess for serious adverse events since the prior study visit. Quality of life assessment will be conducted using the validated EQ-5D-5L tool [38].

